The aim of this trial is to investigate the effect of adding prehabilitation to standard care before TKR, compared with standard care alone, focusing on (1) patient-reported joint awareness 1 year after TKR, and (2) patient enablement and objectively measured knee function 6 weeks after TKR.

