### Sample size

To detect a difference in the MIC of 17.7 points (effect size 0.61) and the MCID of 13.7 points between the SC+P and SC groups in the FJS-12^16^ from baseline to the 52-week follow-up, and assuming a 0.6 proportion of total scores >21 points for the Mod-PEI-2 in the SC+P group versus 0.3 in the SC group at the 6-week follow-up, a total of 110 patients is targeted for inclusion across the two groups (80% power, 5% α-level, with an estimated 20% dropout included).

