### Analysis plan

All analyses will be performed using IBM SPSS Statistics software, V.29, applying intention-to-treat and per-protocol approaches with an α-level of 0.05. Demographic data will be presented as mean or median with SD or IQR for quantitative variables, and as frequencies and percentages for categorical variables.

Depending on measurement scale and distribution, differences between groups at baseline and for primary and secondary outcomes at each follow-up assessment will be analysed using independent samples t-tests or non-parametric equivalent tests. Longitudinal changes within groups from baseline to follow-up time points will be analysed using linear mixed models or generalised linear models, with baseline measurements included as covariates. Multiple linear regression and logistic regression will be used to analyse predictor variables for the primary outcomes (FJS-12 and Mod-PEI-2). Furthermore, analyses of primary and secondary outcomes will be adjusted, if necessary, for differences in intervention delivery and adherence, duration of participation, surgical procedures and postoperative physiotherapy care.

Multiple analyses will be performed using α-level adjustment methods, such as the Bonferroni method. In the intention-to-treat analysis, a sensitivity analysis will be performed to quantify the magnitude of missing data from patients lost to follow-up. Appropriate statistical methods will be used to account for missing data in the analysis, depending on the characteristics of the missing data. If there is extensive missing data, a second table of baseline characteristics will be presented only for patients included in the final analysis. The proportion of missing outcomes per group, characteristics of patients with missing data and possible reasons for missing outcome data will be presented.

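### The FJS-12 sample size refers to a between-arm difference in change from baseline, but the analysis plan compares arms on the outcome at each visit, so the stated 80% power is not established for the planned test

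*Protocol article*

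**What the plan says.** The Sample size section gives two FJS-12 targets. One is worded "To detect a difference in the MIC of 17.7 points (effect size 0.61" and the other is "the MCID of 13.7 points". Both refer to a difference "between the SC+P and SC groups in the FJS-12^16^ from baseline to the 52-week follow-up". It concludes that "a total of 110 patients is targeted for inclusion across the two groups", with "80% power, 5% α-level, with an estimated 20% dropout included". No SD is given, and the article does not say which quantity the effect size standardises. In the same sentence the other primary outcome, Mod-PEI-2, is sized on proportions at one visit (6 weeks after surgery).

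The Analysis plan assigns the between-arm comparison to tests at single visits: "primary and secondary outcomes at each follow-up assessment will be analysed using independent samples t-tests or non-parametric equivalent tests". Change from baseline appears in the next sentence, as "Longitudinal changes within groups from baseline to follow-up time points", to be fitted with linear mixed or generalised linear models that include baseline as a covariate.

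The aim, at the end of the Introduction, speaks of "patient-reported joint awareness 1 year after TKR". Table 3 marks the 52-week visit in bold as a main time point for FJS-12.

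**The concern.** Read literally, the sample size is built on a between-arm difference in change, and its first target is a minimal important change. The analysis section contains no between-arm test of change. It compares arms visit by visit and takes up change only within each arm. The two sections sit next to each other and describe different quantities for the same primary outcome.

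A change and a single-visit score generally have different SDs, so one effect size cannot be carried from one to the other without saying which SD lies behind it. At stake is whether 80% power applies to the comparison that will actually be made. It also matters that the metric be settled in advance, because the Strengths and limitations section says that the trial coordinator and the statistician are not blinded to allocation.

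**Working it through.** **Inputs.** From the Sample size section: difference 17.7 points, effect size d = 0.61, power 80%, α 5%, dropout 20%, total 110. From Randomisation: 1:1 allocation. Assumed, because the article does not give them: a two-sided test, equal SDs at baseline and 52 weeks, and a range for the baseline-to-52-week correlation ρ.

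**Step 1: reproduce the plan's figure.** A two-sample t-test with d = 0.61, two-sided α 0.05 and 80% power needs 44 per arm (noncentral t). Then 2 × 44 = 88, and 88/(1 − 0.20) = 110, exactly as stated. Power at 44 per arm is 0.808. The 110 follows from the 17.7-point target. The 13.7-point target has no effect size of its own and is not part of this point.

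**Step 2: implied SD.** 17.7/0.61 = 29.0. Step 1 is identical whether 29.0 is the SD of the change or of the 52-week score, so reproducing 110 does not show which was meant.

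**Step 3: link the two SDs.** With equal SDs at both visits, SD(change) = SD(score) × √(2(1 − ρ)). The two are equal only at ρ = 0.5. Under randomisation the expected between-arm difference is the same for change and for the 52-week score, so 17.7 is kept throughout and only the SD moves.

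- Reading A, 29.0 is the SD of change: SD(score) = 29.0/√(2(1 − ρ)).
- Reading B, 29.0 is the SD of the 52-week score: SD(change) = 29.0 × √(2(1 − ρ)).
- Baseline-adjusted comparison of the 52-week score: residual SD = SD(score) × √(1 − ρ²), ignoring the one degree of freedom spent on the covariate.

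**Step 4: power at 44 per arm for 17.7 points.**

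| ρ | A: SD of score | A: score test | A: adjusted score | B: SD of change | B: change test | B: adjusted score |
|---|---|---|---|---|---|---|
| 0.2 | 22.9 | 0.947 | 0.955 | 36.7 | 0.609 | 0.823 |
| 0.3 | 24.5 | 0.917 | 0.939 | 34.3 | 0.667 | 0.843 |
| 0.4 | 26.5 | 0.873 | 0.922 | 31.8 | 0.733 | 0.870 |
| 0.5 | 29.0 | 0.808 | 0.904 | 29.0 | 0.808 | 0.904 |
| 0.6 | 32.4 | 0.716 | 0.886 | 26.0 | 0.886 | 0.943 |
| 0.7 | 37.5 | 0.592 | 0.866 | 22.5 | 0.955 | 0.977 |

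Under reading B the test of the 52-week score has power 0.808 whatever ρ is. Over ρ from 0 to 0.8, the lowest power of the adjusted comparison is 0.847 under reading A (at ρ = 0.8) and 0.808 under reading B (at ρ = 0).

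**Step 5: the equal-SD assumption.** If the baseline SD is r times the 52-week SD, SD(change) = SD(52-week score) × √(1 + r² − 2ρr), and the two SDs agree at ρ = r/2. With r = 0.8 under reading A, the score test has power 0.902 at ρ = 0.2, 0.808 at ρ = 0.4 and 0.737 at ρ = 0.5. The crossing point shifts, but the conclusion does not: power may lie above or below 80%.

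**The case against.** The strongest reply is that nothing here shows a deficit. The article never attributes the effect size of 0.61 to change. If it was formed with the SD of the score, the planned 52-week comparison already has 81% power, 110 stands, and the defect is a loose phrase. Many cells in the table exceed 80%. The analysis sentence does not use the word score, and the Abstract lists between-group and within-group tests together without naming a metric. This is also a condensed article, and the source of an SD or the exact primary model may properly sit in an analysis plan that is not shown.

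Most of this stands as a limit on the claim. It does not remove the conflict, which lies in what the article states and not in what it omits: one section gives a difference in change as the basis for sizing, and the next gives the between-arm comparison by visit and confines change to within-arm models.

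Three stronger readings may tempt a reader, and the documents support none of them.

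- That the aim and Table 3 also contradict the sample size. They fix the 52-week time point only and are compatible with either a score or a change.
- That the trial is underpowered, or that the 80% certainly belongs to a quantity never compared between arms. That would require knowing which SD lies behind 0.61, and the article does not say.
- That two between-arm versions of the outcome are planned. As written, the Analysis plan contains one. What stands is that the two sections point to different metrics, so which one is primary is not settled beyond dispute.

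**Conclusion.** The point holds as an inconsistency between the Sample size and Analysis plan sections over the metric of a primary outcome. The stated 80% is not established for the quantity tested. Power of the 52-week score test is 81% if 29.0 is the SD of the score, and 95% to 59% at correlations 0.2 to 0.7 if it is the SD of change. These figures assume 44 evaluable patients per arm, a true difference of 17.7 points, a two-sided 5% test and, for the second range, equal SDs at both visits. The correlation is an assumption, since the article gives none. A loss of power is not shown. The matter is worth correcting because it concerns a primary outcome and can be settled by wording and one calculation.

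**What to change.** In both the Sample size and the Analysis plan sections, name a single primary between-arm analysis for FJS-12: the 52-week score compared between arms with adjustment for baseline FJS-12, and no separate between-arm test of change. Table 3 shows that baseline FJS-12 is already collected, and the plan already uses baseline as a covariate in its within-group models. In the Sample size section, make the FJS-12 difference one at the 52-week follow-up instead of one measured from baseline. State whether the SD of 29.0 describes the score or the change, and restate the power for the adjusted analysis.

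Baseline adjustment also largely removes the score-versus-change question: its power is at least about 0.81 under either reading of the SD for correlations from 0 to 0.8 (equal SDs assumed). The cost is minor rewording and one re-run of the power calculation, with no added patients, visits or data. It should be done before the 52-week results are analysed; the article expects data collection to run to the end of 2027.

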### Randomisation

Patients are randomised using opaque, concealed envelopes and stratified by age (≤67 years, >67 years) with a 1:1 allocation ratio, based on computer-generated random number sequences, into the intervention group, comprising prehabilitation in addition to standard care (SC+P), or the control group, consisting of standard care only (SC). The computer-generated random number envelope sequences were created by a person not otherwise involved in the trial. Allocation is performed by the trial coordinator immediately after the baseline assessment. The trial coordinator did not have access to the randomisation lists before allocation.

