##### Modified Patient Enablement Instrument-2

The modified Patient Enablement Instrument-2 (Mod-PEI-2) is based on the PEI-2, a 6-item PROM in which patients assess their ability to cope with life, understand and manage their disease, maintain health and help themselves. In the original version, patients respond based on information received at a prior doctor’s appointment, whereas in this modified version, patients evaluate their coping abilities over the previous 4 weeks, regardless of any intervention received. Items are rated on a 5-point Likert scale, ranging from ‘extremely well’ to ‘not at all’. Scores are summed to give a total ranging from 6 to 30, with higher scores indicating greater enablement.^41^ Both the Mod-PEI-2 and the Swedish version of the original instrument have demonstrated good validity, reliability, sensitivity and responsiveness, making them suitable for use in intervention studies.^42 43^

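### Mod-PEI-2 is powered as a proportion scoring above 21 but defined as a 6–30 total, and the Analysis plan does not fix which of the two is the primary between-group comparison

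*Protocol article*

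**What the plan says.** All references are to the protocol article.

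- **Sample size.** The Mod-PEI-2 assumption is binary: "assuming a 0.6 proportion of total scores >21 points for the Mod-PEI-2 in the SC+P group versus 0.3 in the SC group". It refers to the assessment six weeks after surgery. Together with the FJS-12 assumption (effect size 0.61), it leads to this target: "a total of 110 patients is targeted for inclusion across the two groups". The conditions attached to that figure are "80% power, 5% α-level, with an estimated 20% dropout included".
- **Modified Patient Enablement Instrument-2** (under Primary outcome measures). The outcome is a score: "Scores are summed to give a total ranging from 6 to 30, with higher scores indicating greater enablement". No threshold is given.
- **Analysis plan.** Group differences for "primary and secondary outcomes at each follow-up assessment will be analysed using independent samples t-tests or non-parametric equivalent tests". The sentence opens by making the choice depend on the scale and distribution of the measure. Linear mixed or generalised linear models are named for change within groups. Linear and logistic regression are named for predictors of FJS-12 and Mod-PEI-2. No comparison of two proportions between arms is named.
- **Table 3.** The 6-week visit is marked as the main time point for Mod-PEI-2, and the instrument is also completed at baseline.

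**The concern.** A power statement should describe the comparison that will be made. Here it describes a difference in responder proportions, while the outcome definition and the named between-group tests point to a difference in scores. No assumed difference or SD is given for the total, so its power cannot be read from the document.

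The larger issue is reporting. With both forms open, the score result or the responder result could be presented as primary after the data are seen. The Strengths and limitations section says that the trial coordinator and the statistician are not blinded to allocation, so it matters more that the choice is fixed in advance.

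**Working it through.** **Inputs.** From Sample size: proportions 0.6 and 0.3, FJS-12 effect size 0.61, 80% power, 5% alpha (taken as two-sided, since sidedness is not stated) and 20% dropout. From Randomisation: allocation "with a 1:1 allocation ratio". Completers per arm: 110 × 0.8 / 2 = 44.

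**1. Reproducing the 110.**
- FJS-12, two-sample t-test at d = 0.61: 44 per arm for 80% power, and 88/0.8 = 110 exactly.
- Mod-PEI-2 as two proportions, mean proportion 0.45: n = [1.960 × √(2 × 0.45 × 0.55) + 0.842 × √(0.6 × 0.4 + 0.3 × 0.7)]² / 0.3² = (1.379 + 0.565)² / 0.09 ≈ 42.0, so 42 per arm, and 84/0.8 = 105.

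FJS-12 therefore sets the total, and the Mod-PEI-2 assumption fits under it.

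**2. Power for the proportion at 44 per arm.**
- Alpha 0.05: z = (0.3 × √44 − 1.379)/0.671 = 0.911, so 81.9%. The exact binomial power of the chi-square test is 81.1%.
- Alpha 0.025 (0.05 halved for two primary outcomes; critical value 2.241): z = (1.990 − 1.577)/0.671 = 0.616, so 73.1%. The exact figure is 73.2%.

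**3. Power for the total at 44 per arm.** Assume a normal total with equal SDs and a shift that yields 0.6 v 0.3 above a common cut-off.
- d = z(0.6) − z(0.3) = 0.253 + 0.524 = 0.778 SD.
- n = 2 × (1.960 + 0.842)² / 0.778² ≈ 26 per arm, or 27 with the t distribution.
- Noncentrality at 44 per arm is 0.778 × √22 = 3.65. Power is 95.0% at alpha 0.05 and 91.2% at 0.025.

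**4. Sensitivity to the normal assumption.** On a logistic scale the log odds ratio is ln(0.6/0.4) − ln(0.3/0.7) = 1.253. Dividing by π/√3 = 1.814 gives d = 0.691.
- t-test: 2 × (2.802)² / 0.691² ≈ 33 per arm.
- Rank test under proportional odds: 6 × (2.802)² / 1.253² ≈ 30 per arm.
- t-test power at 44 per arm, with noncentrality 0.691 × √22 = 3.24: about 89% at alpha 0.05 and 83% at 0.025.

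**5. Efficiency loss from dichotomising, against 42 per arm.**

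| Model for the total | n per arm | Reduction |
|---|---|---|
| Normal, normal approximation | 26 | 38% |
| Normal, t-test | 27 | 36% |
| Logistic, rank test | 30 | 29% |
| Logistic, t-test | 33 | 21% |

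**The case against.** The strongest reply is that the plan already allows a binary analysis. The choice of test depends on the measurement scale, and logistic regression is listed for the primary outcomes, Mod-PEI-2 included. A total above 21 is built from the same 6–30 sum, so the instrument description does not rule it out. A responder endpoint is a legitimate choice, and a condensed article may leave the exact test to an analysis plan that is not shown.

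Much of this stands. A reader might infer that the trial is powered for a test it will not run. The document does not support that, because it never says that Mod-PEI-2 is analysed only as a total. What it supports is narrower: the responder comparison is not specified as the between-group analysis, and the text assigns logistic regression to predictors rather than to the treatment effect. The point does not depend on missing detail either, since the article commits to a binary basis in one section and to score-type tests in another.

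A reader might also infer that dichotomising wastes about a third of the sample. That does not follow. If the total is analysed, nothing is dichotomised. If the proportion is analysed, the patients are needed for FJS-12 anyway.

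**Conclusion.** The mismatch is real, and the Sample size, outcome definition and Analysis plan sections need to be reconciled. The sample size of 110 stands, and the trial is not underpowered for Mod-PEI-2 on this account: at 5% alpha either form reaches the stated 80%, and moving to the total raises power under every distribution tried.

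The choice between forms has a practical effect only if alpha is split. The Analysis plan mentions Bonferroni-type adjustment without saying whether it covers the two primary outcomes. If it does, the proportion falls below 80% while the total stays above it.

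The figures for the total rest on an assumed shift model, because the article gives no SD or distribution for Mod-PEI-2. The efficiency loss of 21–38% depends on that model and does not change the planned size. What is at stake is an undeclared choice between two versions of one primary result, not lost patients.

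**What to change.** Name one primary Mod-PEI-2 variable and its between-group test.

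- **Preferred:** the total at 6 weeks after surgery, compared between arms in a linear model adjusted for the baseline total and for the age stratum used in randomisation. This agrees with the outcome definition, and both covariates are already collected.
- **Proportion above 21:** report it as a supportive description, with the reason for the cut-off.
- **Power statement:** restate it for the chosen comparison. For the total, give the assumed difference in points and the SD. The present assumption corresponds to 0.78 SD under normality. State the alpha that applies to this outcome.

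If the authors prefer the responder form, the same clarity is needed: make it the stated primary variable, name its between-group test and justify the cut-off.

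The cost is wording only, with no new data and no change to the 110. Recruitment is expected to run through 2026 and data collection to the end of 2027, so the clarification can be dated and recorded with the other protocol changes well before analysis.

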### Analysis plan

All analyses will be performed using IBM SPSS Statistics software, V.29, applying intention-to-treat and per-protocol approaches with an α-level of 0.05. Demographic data will be presented as mean or median with SD or IQR for quantitative variables, and as frequencies and percentages for categorical variables.

Depending on measurement scale and distribution, differences between groups at baseline and for primary and secondary outcomes at each follow-up assessment will be analysed using independent samples t-tests or non-parametric equivalent tests. Longitudinal changes within groups from baseline to follow-up time points will be analysed using linear mixed models or generalised linear models, with baseline measurements included as covariates. Multiple linear regression and logistic regression will be used to analyse predictor variables for the primary outcomes (FJS-12 and Mod-PEI-2). Furthermore, analyses of primary and secondary outcomes will be adjusted, if necessary, for differences in intervention delivery and adherence, duration of participation, surgical procedures and postoperative physiotherapy care.

Multiple analyses will be performed using α-level adjustment methods, such as the Bonferroni method. In the intention-to-treat analysis, a sensitivity analysis will be performed to quantify the magnitude of missing data from patients lost to follow-up. Appropriate statistical methods will be used to account for missing data in the analysis, depending on the characteristics of the missing data. If there is extensive missing data, a second table of baseline characteristics will be presented only for patients included in the final analysis. The proportion of missing outcomes per group, characteristics of patients with missing data and possible reasons for missing outcome data will be presented.

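### The analysis plan significance-tests baseline differences between randomised arms; these tests cannot show comparability and should give way to descriptive reporting and prespecified baseline adjustment

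*Protocol article*

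**What the plan says.** The Analysis plan states that "differences between groups at baseline and for primary and secondary outcomes at each follow-up assessment will be analysed using independent samples t-tests" or non-parametric equivalents, depending on scale and distribution. Analyses are run "applying intention-to-treat and per-protocol approaches with an α-level of 0.05".

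Three neighbouring statements bear on this:

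- Descriptive reporting is already planned: "Demographic data will be presented as mean or median with SD or IQR for quantitative variables", with counts and percentages for categorical variables. The baseline tests come on top of that.
- "Multiple analyses will be performed using α-level adjustment methods, such as the Bonferroni method". The analyses that make up this family are not named.
- The longitudinal models are fitted "with baseline measurements included as covariates", but that sentence concerns change within groups. The between-group comparisons at follow-up are described as two-sample tests.

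Under Randomisation, allocation is "based on computer-generated random number sequences", delivered in opaque concealed envelopes and "stratified by age (≤67 years, >67 years) with a 1:1 allocation ratio". The trial coordinator allocates directly after the baseline assessment and has not seen the lists.

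**The concern.** A test of a baseline difference between randomised arms asks whether chance explains it. For anything measured before a sound, concealed allocation, the answer is known beforehand: it does. A small p-value is then a false alarm. A large one says only that the difference was not large relative to its standard error, which is not the same as being too small to matter for the outcome.

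Two things are at stake. The report may call the arms unbalanced because of one stray p-value, or balanced because there was none, and neither statement would be sound. Further, if the baseline tests count among the multiple analyses to be corrected, they use up significance level that the outcome comparisons need.

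**Working it through.** **Inputs**

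- Sample size section: "a total of 110 patients is targeted for inclusion across the two groups". At 1:1 this is 55 per arm at baseline.
- Analysis plan: α = 0.05 per test (two-sided assumed; sidedness is not stated).
- Table 3: nine instruments have a baseline entry (FJS-12, Mod-PEI-2, KOOS, IPAQ-sf, EQ-5D-3L, quadriceps strength, knee ROM, 30s CST, activPAL). The number of tests is not stated. Counting KOOS as five subscales (an assumption) and ROM as flexion and extension gives 9 + 4 + 1 = 14. Demographic, lifestyle and expectation items could bring it to 20 (also an assumption).

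**The plan's own figure.** With d = 0.61, two-sided 5% and 80% power, the t-based calculation gives 44 per arm. That is 88 in total, and 88/0.8 = 110, so the stated total is reproduced.

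**What a baseline test can detect.** The standard error of a standardised difference is √(2/55) = 0.191. The smallest difference with p<0.05 is t(0.975; 108) × 0.191 = 0.378 SD.

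- An observed 0.30 SD imbalance gives t = 0.30/0.191 = 1.57 and p = 0.12. At 0.35 SD, p = 0.07. Both would be reported as no difference.
- By chance alone, a given variable shows an imbalance above 0.20 SD with probability 0.294 and above 0.378 SD with probability 0.047 (normal approximation). The chance of an unflagged imbalance between the two is 0.294 − 0.047 = 0.247, about 25%.

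**Chance of at least one false flag.** For k independent tests it is 1 − 0.95^k uncorrected, and 1 − (1 − 0.05/k)^k under Bonferroni. The correlated columns come from simulation with equal correlation between all tests.

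| k | Independent | Correlation 0.3 | Correlation 0.5 | Bonferroni |
|---|---|---|---|---|
| 9 | 37% | 33% | 27% | 4.9% |
| 14 | 51% | 44% | 35% | 4.9% |
| 20 | 64% | 54% | 42% | 4.9% |

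Bonferroni removes most false flags but makes the tests less sensitive still. Over 20 tests the threshold rises from 0.378 SD to about 0.59 SD.

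**What an imbalance does to an unadjusted follow-up comparison.** With baseline-to-outcome correlation r (not in the document; 0.3 to 0.5 assumed) and equal SDs, a 0.30 SD imbalance shifts a comparison of follow-up scores by r × 0.30, which is 0.09 to 0.15 SD. In change scores the shift is (r − 1) × 0.30, which is −0.21 to −0.15 SD. Either shift occurs whether or not baseline is tested. Only adjustment for the baseline score deals with it.

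**The case against.** The strongest reply is that this is a reporting convention: the tests alter neither the primary estimate, nor the covariates, nor the sample size. Much of that stands, and four stronger readings should be set aside.

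- *Baseline p-values will choose the covariates.* A reader might infer this from the provision for adjustment where needed and from the unblinded statistician listed under limitations. The adjustment sentence, however, lists intervention delivery and adherence, duration of participation, surgery and postoperative physiotherapy. All of these arise after randomisation, and baseline imbalance is not among them.
- *A false imbalance is more likely than not.* This needs at least 14 independent, uncorrected tests. The nine listed instruments give 37%, measures of the same knee are likely to be correlated, and Bonferroni would bring the figure to about 5%. A large false-flag risk and an enlarged multiplicity family are also alternatives: the first arises if the tests are uncorrected, the second if they are inside the correction. The article does not say which applies.
- *The tests bias the FJS-12 result.* The shift shown above comes from leaving the follow-up comparison unadjusted, so deleting the tests alone would not remove it.
- *The 0.38 SD threshold equals 11 FJS-12 points.* That uses the implied SD of 17.7/0.61 = 29.0. The sample size section frames the difference as running from baseline to 52 weeks, so this may be an SD of change. No baseline SD is given.

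It can also be said that the tests might expose a breakdown of envelope concealment. That is why the claim here is conditional on randomisation working as described. A set of p-values with a 0.38 SD threshold is still a weak audit. The activPAL measure is a separate exception: its baseline week begins at the baseline visit and so continues after allocation. A difference there could be a real early response, but it would not be an allocation imbalance either.

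**Conclusion.** The concern holds in limited form. The article states a plan to significance-test baseline differences between concealed, randomised arms. For measures taken before allocation, these tests can only flag chance if randomisation works as described. With 55 per arm and two-sided 5% tests they miss any imbalance below about 0.38 SD, so a non-significant result is no evidence of comparability.

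How often they raise a false flag cannot be fixed from the article, because it rests on an unstated number of tests, their correlation and the scope of the correction. Across the cases tabulated, the range is about 5% to 64%.

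The consequence is misleading statements about balance and, if baseline tests fall within the correction, a larger multiplicity family. The document does not support a claim that the primary estimate is biased by this step.

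**What to change.** In the Analysis plan:

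1. Remove baseline from the sentence listing the comparisons to be tested.
2. State that baseline characteristics and baseline outcome scores are presented by arm descriptively, without p-values. Standardised differences may be added if wanted.
3. State that baseline comparisons are outside the multiplicity family.
4. Prespecify that between-group follow-up comparisons are adjusted for the baseline value of the outcome, where one is measured, and for the age stratum, whatever imbalance is observed. Satisfaction has no baseline value, so only the stratum applies there.

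Step 4 is needed because steps 1 to 3 tidy the reporting but leave a chance imbalance in the outcome comparison.

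The cost is a few sentences. No new data are needed, the target of 110 is unchanged, and no information is lost. The article expects recruitment throughout 2026 and data collection to the end of 2027, so on that timetable the change can be made before analysis.
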